### Intervention

The initial purpose of the Stadsscholen020 intervention program initiated by the municipality of Amsterdam is to promote equal chances for a successful educational career for all children who grow up in Amsterdam regardless their ethnic background, family situation, and neighborhood. The intervention period of Stadsscholen020 is two school years starting in September 2016 until July 2018. The intervention started right after the pilot phase during school year 2015–2016 which can be seen as an orientation period for introducing and developing the activities of Stadsscholen020. The primary schools participating in this school-based interdisciplinary intervention approach received a financial impulse to have extra resources for the three following domains: Supporting the school team, Improving student learning, and Supporting and creating more resources around the school.

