#### Part II. Cross-sectional study

Complementary to the individual data and detailed information from the longitudinal and process evaluation, the cross-sectional study will include data from public databases of the municipality of Amsterdam (Onderzoek, Informatie en Statistiek, OIS), the Public Health Service of Amsterdam (GGD), and The Education Executive Agency of the Dutch Ministry of Education, Culture, and Science (Dienst Uitvoering Onderwijs, DUO). These data will be used to observe the effects of Stadsscholen020 during the intervention period on determinants related to health, poverty, and academic achievement that are available on school and neighborhood level. Data from the schools and the neighborhood where the schools are located (Amsterdam Holendrecht) will be compared with data on a wider district and city level. Table 2 shows the overview of the indicators related to the primary and secondary outcomes that will be examined in this cross-sectional study.

**Table 2 Tab2:** Overview of primary and secondary outcomes, indicators, and measurements

	Informants	Study parts		
		Longitudinal study *5 assessments*	Cross-sectional study *5 year period*	Process evaluation *5 assessments*
*Child Health*				
Life satisfaction (Cantril Ladder)	Child	×	×	
Socioemotional Well-being (SDQ)	Child	×		
Quality of life (KIDSCREEN)	Child	×		
Sport club membership	Child	×		
Dietary behavior (daily warm meal and fruit intake questions)	Child	×		
% 5-years old / 10-years old children with overweight (including obesity)	GGD		×	
% 5-years old / 10-years old children having breakfast every day	GGD		×	
% 5-years old / 10-years old children eating greens every day	GGD		×	
% 5-years old / 10-years old children that is physical active	GGD		×	
% Households supported by child welfare organizations (OKT)	GGD		×	
*Child Poverty*				
Family Affluence (FAS)	Child	×		
Stadspas ownership (minimal income permit)	Child	×		
% Households depending on social security benefits	OIS		×	
% Households having an income up to 120% of the social minimum	OIS		×	
% Children having parents with a lower education	OIS		×	
*Child Academic Achievement*				
Secondary school qualifications	DUO		×	
School test results (CITO)	DUO		×	
*School Environment*				
Teacher self-efficacy (TSES)	Teacher			×
Classroom climate (Class climate scale)	Teacher			×
School and neighborhood safety (additional questions)	Child			×
Bullying (KIDSCREEN and additional questions)	Child			×

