#### Data analysis

To investigate whether the Stadsscholen020 program leads to significant changes on primary and secondary outcomes over time, repeated measures ANOVAs and linear mixed models analysis techniques will be performed for this the longitudinal data. The linear mixed models technique is able the handle missing data using a likelihood based approach, every observation for every participant is used, irrespective of their missing data. The appropriate covariance structure, which accounts for the within-subject correlation, will be chosen based on the model fit using the − 2 log likelihood value. Cross-sectional data will be analysed by comparing means between the different levels (school, neighbourhood, district, and city level) using independent *t*-tests and ANOVA.

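### Part II's stated analysis compares levels only, over an unnamed five-year window, and so does not separate the two programme years from the others

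*Protocol article*

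**What the plan says.** Four statements in the protocol article bear on this point.

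- **Aim** (Part II. Cross-sectional study): "These data will be used to observe the effects of Stadsscholen020 during the intervention period".
- **Dates** (Intervention): "The intervention period of Stadsscholen020 is two school years starting in September 2016 until July 2018". The school year before that, 2015–2016, was a pilot, "which can be seen as an orientation period for introducing and developing the activities of Stadsscholen020".
- **Data window** (Table 2): the Part II column is headed "Cross-sectional study *5 year period". No start or end year is given.
- **Comparison**: Part II says that school and neighbourhood data "will be compared with data on a wider district and city level". The Data analysis section adds: "Cross-sectional data will be analysed by comparing means between the different levels". The levels are school, neighbourhood, district and city, and the methods are independent t-tests and ANOVA. No year, period or before/after term is named for Part II. In the same section, the longitudinal data are to be analysed for change over time.

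**The concern.** The aim concerns two school years and the data cover five. The one stated analysis looks across levels and not across time, so nothing in it distinguishes a year in which the programme ran from one in which it did not.

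Averaging over years is a plausible way to carry out such an analysis. Many Part II indicators in Table 2 are percentages taken from public databases. If only one aggregate percentage per level and year is available, a t-test or ANOVA between levels needs replicate values, and the yearly figures are the obvious source. Programme and non-programme years would then enter the same mean.

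Both quantitative indicators listed for child academic achievement in Table 2 (secondary school qualifications and school test results) are assessed only in Part II. That secondary outcome therefore depends largely on this comparison, as do the overweight and household-income indicators.

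**Working it through.** The article gives no sample size, effect size or power for Part II, so there is no figure of its own to reproduce. The check is date arithmetic, followed by what each way of using the years would estimate.

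**1. Share of the window covered by the programme.** Take 1 September 2016 to 31 July 2018 (the article gives months only; the days are my assumption).
- Days: 122 (2016) + 365 (2017) + 212 (2018) = 699.
- Years: 699 / 365.25 = 1.91.
- Share of five years: 1.91 / 5 = 0.38.
- In school years: 2 of 5 = 0.40. At least three of any five school years lie outside the stated period.

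**2. Shift that remains if the five years are averaged.** Assume that the window contains both programme years and that the programme moves the indicator by a constant d in each exposed year and by 0 otherwise.

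| How exposed years are counted | Share of d left in the five-year mean |
|---|---|
| Two programme school years | 2/5 = 0.40 |
| Exact dates, or calendar years in proportion (0.33 + 1.00 + 0.58 = 1.91) | 1.91/5 = 0.38 |
| Pilot year counted as fully exposed | 3/5 = 0.60 |
| All three calendar years touched (2016, 2017, 2018) counted as fully exposed | 3/5 = 0.60 |

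**3. Shift that remains if years are kept separate.** Mean of programme years minus mean of pre-programme years = d − 0 = d, or 100%. There is no dilution.

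**4. What a comparison between levels estimates.** Let G be the difference between Holendrecht and the city that exists without the programme. The article describes the neighbourhood as deprived, so G is unlikely to be zero.
- Five years averaged: G + 0.4d.
- Programme years only: G + d.
- Programme years minus pre-programme years, then compared between levels: (G + d) − G = d, provided G would otherwise have stayed constant.

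Only the third isolates d, and it needs a period term.

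**5. Why the identity of the five years matters.** These are the five-school-year windows that contain both programme years:

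| First school year | Before | Pilot | Programme | After |
|---|---|---|---|---|
| 2013–2014 | 2 | 1 | 2 | 0 |
| 2014–2015 | 1 | 1 | 2 | 1 |
| 2015–2016 | 0 | 1 | 2 | 2 |
| 2016–2017 | 0 | 0 | 2 | 3 |

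Only the first two contain a pre-programme year. The article does not say which window applies.

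**The case against.** The strongest reply has three parts.

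*The texts do not contradict each other.* A reader might infer that Part II is confined to 2016–2018 and that Table 2 breaks this limit. The documents do not support that. The aim says when effects are looked for, not which years of data may be used. Seeing an effect in 2016–2018 requires years outside it for reference, and cutting the window to two years would remove them. This part stands in full.

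*Averaging is never stated.* A reader might also infer that the plan will dilute any effect on every Part II indicator, or lose a fixed share of its signal-to-noise ratio. Table 2 gives a span of data and no averaging rule, and the Data analysis section does not say that years are combined. A signal-to-noise figure would further need independent yearly values of equal scatter and the full effect from the first programme year. The Discussion says that it is unknown how long changes take to appear. This part also stands, so the dilution figures are conditional.

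*This is a condensed article.* Which years of public data enter, and how they are labelled, may be set out in a fuller document. That is fair for the year labels alone. It does not cover the rest: the article does state an analysis for Part II, and that analysis, a comparison of levels without any period term, does not serve the aim stated for the same part.

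**Conclusion.** The concern holds in a limited form. The five-year window is acceptable. The stated analysis is the weak point, because comparing levels over an unnamed five-year span does not separate programme years from the others, and a difference between levels also contains whatever gap existed beforehand.

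The size depends on an unstated choice. If the years were averaged, about 40% of a constant programme-year shift would remain (38% to 60% across the definitions above). If they are kept separate, the loss is zero. The 40% assumes that both programme years fall in the window and that the shift is the same in each. The documents do not establish that dilution will occur, nor by how much on any given indicator.

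The change should be made: the reading in which the extra years serve as reference is sensible, but it too requires labelled years and a period contrast, and the article states neither.

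**What to change.** Keep the five-year window and change the wording in two places.

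- **Table 2 and the Part II text:** name the five years and label each as before, pilot (2015–2016), programme (2016–2017 and 2017–2018) or after. Confirm that at least one year before the pilot is included. State for each indicator whether it is reported by school year or by calendar year.
- **Data analysis:** replace the level-only comparison with one that contrasts programme years with pre-programme years at each level, and compare that change between the schools or neighbourhood and the district and city. Show the pilot year separately, in neither period. For calendar-year indicators, flag 2016 and 2018 as partial programme years.

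The public sources are the same, so the direct cost is rewording. The statistical cost is fewer data points: two school years in the programme period and, if both are in the window, at most two before the pilot. Intervals will be wider than those from five averaged years.

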#### Part III. Process evaluation

Since Stadsscholen020 is a complex interdisciplinary approach with a large variety of activities and interventions, a process evaluation will help to provide more detailed information about the effectiveness of the program. The process evaluation will be conducted to provide insight on the reach, acceptance, implementation, and feasibility of the intervention at the schools. Also, the process evaluation will give guidance for future successful implementation of intervention components at other schools and neighbourhoods in the Netherlands. Thereby, the process evaluation will help to understand the findings from the longitudinal and cross-sectional study parts.

Part of the process evaluation will include a detailed description of all the interventions and activities at the four schools initiated with the supplemental financial resources. With regards to the effectiveness of Stadsscholen020 this description provides information about the mechanisms that impact the outcomes. The process evaluation will include both quantitative and qualitative methods. Qualitative interviews with the policy and practice stakeholders, members of the school team, and parents. For example, the school boards will be interviewed several times during the intervention period to reflect on the implementation process of the program. Also, the potential benefits for the school, teachers, and children are discussed in this interview. Additionally, project members and policy makers of the municipality of Amsterdam will be interviewed about their experiences with Staddscholen020. These qualitative interviews will be recorded, transcribed, and subsequently coded using qualitative data analysis software (MAXQDA). In addition to the qualitative interviews, the documentary collected during the intervention period will be analysed. These documentary includes policy documents, minutes of meetings, and self-administered logs of observations conducted by the research team.

Quantitative data for the process evaluation will be collected from children and teachers with regards to the school environment as a mechanism that impact the outcomes on child health and academic achievement. In joined collaboration with involved parents at the schools, supplementary questions on the school- and neighbourhood safety are included in the child questionnaire. Also, two subscales of the KIDSCREEN (School Environment and Bullying) are used to obtain information about the school environment. With regards to the teacher’s perception of the school environment, the following two questionnaires are additionally administered:

##### III.1 School Environment

*Teacher Self-efficacy.* School performance of children can be positively affected by the teacher’s self-efficacy [30]. Therefore, we will use teacher self-efficacy as in indicator of child academic achievement. The Dutch translation of the Teacher Sense of Efficacy Scale (TSES) is used [31, 32]. The TSES measures the teachers’ perceptions of their competence across a range of teaching tasks. For the current study we use the shortened version that consists of 12 items. Items are rated at a 7-point scale, ranging from 1 (*nothing*) to 7 (*a great deal*). Psychometric properties of the TSES have been found adequate [32].

*Classroom climate.* The ‘Klimaatschaal’ (Class climate scale) is a Dutch questionnaire to measure the classroom’s pedagogical environment assessed by teachers [33]. There are four dimensions that constitute the pedagogical environment: Quality of Mutual Student Relationships, Class Atmosphere, Enforcement, and Quality of the Student-teacher Interaction. The questionnaire consists of 33 items rated at a 4-point scale (1 = *[almost] never*, 2 = *sometimes*, 3 = *regularly*, 4 = *always*). The ‘Klimaatschaal’ has adequate psychometric properties [33].

### Statistical analyses

#### Power calculation for the primary outcome

At the start of our study the four schools have respectively 82, 119, 121, and 155 children in the targeted groups (Group 5 to 8; 477 children in total for the four schools). Because each school has different activities and interventions related to the Stadsscholen020 program we conducted a power calculation to estimate the sample size per school to ensure there is enough power to detect intervention effects over time. For this power calculation we used the general health-related quality of life in children (KIDSCREEN-10 index) as an indicator of our primary outcome Child Health. Using norm data [26] and pilot data from our sample we calculated that an effect size of 0.70 is related to a relevant change. Based on Cohen’s *d* this effect size is viewed as a large effect [34]. A sample size of 56 children per school was required to detect this effect size with 95% power when using a repeated measures ANOVA (within-between interaction) and a significance level (α) of 0.05. In correspondence with the stakeholders involved in this research project we accounted for an expected 30% dropout rate including both study dropout and natural dropout due to school change or migration. Therefore, the sample size per school is estimated at 73 children per school. Based on this power calculation we assume that the initially targeted population at baseline (*N* = 477) at the four schools is sufficient to detect a relevant change on the primary outcome measure.

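### The 95% power is attached to a within-between interaction, but all four schools get the programme and the stated question is change over time, so the figure belongs to a different hypothesis

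*Protocol article*

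**What the plan says.** Under Power calculation for the primary outcome, the article gives the purpose of the calculation: "we conducted a power calculation to estimate the sample size per school to ensure there is enough power to detect intervention effects over time". The reason for working per school is that activities differ between schools. The indicator is the KIDSCREEN-10 index, and on the effect size the article says "we calculated that an effect size of 0.70 is related to a relevant change", read on Cohen's *d* scale. It continues: "A sample size of 56 children per school was required to detect this effect size with 95% power". The same sentence names the test to which that power is attached: "with 95% power when using a repeated measures ANOVA (within-between interaction) and a significance level" of 0.05. The paragraph concludes that the 477 children at baseline are enough to detect a relevant change.

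The Data analysis section states its aim as follows: "To investigate whether the Stadsscholen020 program leads to significant changes on primary and secondary outcomes over time". It names repeated measures ANOVAs and linear mixed models, and does not say which model term carries the conclusion.

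Design and study setting, Eligibility criteria and Intervention describe four schools in one neighbourhood, all of them in the programme. The comparison with district and city belongs to Part II, which uses aggregate public data. In Table 2 the KIDSCREEN quality-of-life measure is marked for the longitudinal part, and its School and Bullying subscales for the process evaluation. It is not marked for Part II.

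**The concern.** A within-between interaction answers whether groups change differently. It measures a programme effect when one group is treated and another is not. In Part I nobody is untreated. The article leaves the between factor unnamed, but its per-school rationale points to school. Grade or cohort would not isolate the programme either, because those children are all exposed too.

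With school as the factor, the null hypothesis of the interaction is equal change in all four schools. That null is true when the programme does nothing, and equally true when it helps every school by the same amount. The interaction can also be significant when the average change is zero.

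The only power figure in the article is therefore tied to a hypothesis other than the one set out in either section. A reader who takes the 95% as the chance of detecting a relevant improvement is misinformed about what was calculated. An analyst who takes the power paragraph as naming the primary test would look at the wrong term.

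**Working it through.** **Inputs from the article.** Alpha 0.05; power 95%; effect size 0.70; 56 per school; four schools with 82, 119, 121 and 155 children (477 in total); five assessments. **Not in the article, so assumed.** Within-child correlation rho (0 to 0.5 below), SD of 1 at each wave, and school as the between factor.

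**1. Reproducing the 56.** For two groups, d = 0.70 corresponds to f = 0.70/2 = 0.35. The article does not give the number of groups k, the number of measurements m, or rho for this calculation. Several settings lead to 56:

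| Noncentrality | k | m | rho | Result at 95% power |
|---|---|---|---|---|
| f²(N−k)(m−1) | 2 | 2 | not used | N = 112, i.e. 56 per group |
| f²Nm/(1−rho) | 2 | 2 | 0 | N = 56 in total |
| f²Nm/(1−rho) | 4 | 2 | 0.3 | N = 56 in total |
| f²Nm/(1−rho) | 4 | 3 | 0.1 | N = 56 in total |

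The figure can be reached, but the settings actually used cannot be confirmed. Nothing below depends on them.

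**2. Power of school x time.** For two waves with n children per school, let δ_j be the mean change in school j. The noncentrality is

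λ = n Σ(δ_j − δ̄)² / [2(1−rho)].

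If every school gains 0.70 SD, each deviation is zero, so λ = 0 and power equals alpha, 5%. This holds for any n, rho or number of waves.

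Other patterns, with n = 56 and rho = 0.5, so that 2(1−rho) = 1:

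- One school +0.70, three at 0: mean 0.175; λ = 56 × (0.525² + 3 × 0.175²) = 56 × 0.3675 = 20.6; power about 98%.
- Changes of 0.5, 0.6, 0.7 and 0.8: λ = 56 × 0.05 = 2.8; power about 25%.
- Two schools +0.35, two −0.35: mean zero; λ = 56 × 4 × 0.35² = 27.4; power above 99%.

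**3. Check by simulation** (56 per school, rho 0.5, 4,000 runs):

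| True change by school | Waves | school x time significant | time effect significant |
|---|---|---|---|
| +0.70 in all four | 2 | 5.3% | 100% |
| +0.70 in all four | 5 | 5.1% | 100% |
| +0.70 in all four, actual school sizes | 2 | 4.7% | 100% |
| +0.70 in one, 0 in three | 2 | 97.9% | 74.2% |
| 0.5, 0.6, 0.7, 0.8 | 2 | 25.6% | 100% |
| +0.35 in two, −0.35 in two | 2 | 99.8% | 5.1% |

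The two tests respond to different things.

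**4. Power of the time effect in one school.** Paired comparison of two waves, two-sided alpha 0.05, n = 56:

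d_z = 0.70/√[2(1−rho)], noncentrality = d_z√56, critical t(55) = 2.004.

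- rho = 0: d_z = 0.495, noncentrality 3.70, power 95.3%.
- rho = 0.5: d_z = 0.70, noncentrality 5.24, power 99.9%. At this correlation, 29 children already give 95%.

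So the planned 56 per school serves the time question at least as well as the article claims.

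**The case against.** **Schools differ by design.** Each school chooses its own activities, so whether they differ in change is a fair question, and exactly equal improvement is an extreme case. This stands in part: the interaction has a place, and it would be too strong to call it a question of no interest here. But differing activities are a reason to report each school. They do not turn a test of differences between schools into a test of whether children's health changes, and both sections state the latter. Nor is exact equality needed for the problem to show: gains of 0.5 to 0.8 in every school leave the interaction at about 25% power.

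**Data analysis already asks about change over time.** This stands. A reader might infer that a programme helping all four schools would be declared ineffective. The article does not support that: it nowhere names the interaction as the deciding test, and the detailed model terms may sit in an analysis plan that is not shown. What remains is not an omission, because the article names a specific test and attaches 95% power to it.

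**The sample is adequate anyway.** This also stands. All Group 5 to 8 children in the four schools are approached, so the calculation does not set recruitment, and 56 per school is enough for the time effect.

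**The 56 must be an error.** A reader might also infer that 56 cannot come from four schools, or only from two measurements with zero correlation. Step 1 of the working shows otherwise, so no claim is made about its origin.

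**Conclusion.** The concern holds as a mismatch between the powered test and the stated question. With school as the between factor, the named interaction has 5% power when all four schools improve equally. This follows from its null hypothesis and rests on no assumed figure except the choice of factor, which the article leaves unnamed. The time effect in the same situation has power close to 100% pooled, and 95% to 99.9% within one school of 56 for assumed correlations of 0 to 0.5.

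The consequence is a power statement that cannot be relied on as written, together with uncertainty over which term answers the primary question. It is not a shortage of children, and it does not show that the analysis will reach a wrong conclusion. It should be fixed, but it does not undermine the study.

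Correcting the test does not supply a control group. A time effect in four treated schools still cannot separate the programme from ageing or secular change. The Discussion already concedes that causal relationships are difficult to determine.

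**What to change.** **Power calculation for the primary outcome.** Replace the within-between interaction with the within-child time (wave) effect on the KIDSCREEN-10 index. This can be done per school, which fits the paragraph's own rationale, or pooled with school as a fixed effect, or both; either repairs the mismatch. State which waves are compared, the assumed within-child correlation, and the expected n for that comparison. The last matters because Table 1 shows only cohorts C and D assessed at both T1 and T5. Possible wording for the two-wave, per-school case: 56 children give about 95% power for a 0.70 SD change if the correlation is 0, and 99.9% if it is 0.5, both values being assumptions.

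**Data analysis.** Add that the time effect answers the primary question, and that school x time is secondary and tests whether schools differ in change.

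**Cost.** One rewritten paragraph and one added sentence. The correction needs no extra children and no new data.

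### The 30% dropout allowance is applied by multiplying by 1.3, giving 73 per school; keeping 56 children needs 56/0.70 = 80, which all four rolls still exceed, the smallest by only 2

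*Protocol article*

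**What the plan says.** The calculation is in the Protocol article, Power calculation for the primary outcome. It is done per school because the schools run different activities, and it uses the KIDSCREEN-10 index as the indicator of child health.

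- Requirement before losses: "A sample size of 56 children per school was required to detect this effect size with 95% power".
- Test: the calculation applies "when using a repeated measures ANOVA (within-between interaction) and a significance level (α) of 0.05".
- Losses: "we accounted for an expected 30% dropout rate including both study dropout and natural dropout due to school change or migration".
- Result: "Therefore, the sample size per school is estimated at 73 children per school".

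The section also reports that "the four schools have respectively 82, 119, 121, and 155 children in the targeted groups", 477 in total, and judges this baseline population sufficient. Under Participants and recruitment, all children in Groups 5 to 8 are invited, and parents may opt their child out.

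**The concern.** The required number, the dropout rate and the resulting number are all printed, and they do not agree. Adding 30% to 56 is not the same as allowing for 30% of the starters to be lost. The first gives 73; the second needs a larger start.

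The per-school figure is the yardstick against which the plan judges the four rolls. If it is too low, a school can appear to have a comfortable reserve when it has almost none. The smallest school, with 82 children, is the only one where the difference could matter.

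**Working it through.** **Inputs**, all from Power calculation for the primary outcome: required n = 56 per school; dropout = 30%; stated inflated n = 73; rolls = 82, 119, 121 and 155; effect size 0.70; power 95%; α = 0.05, sidedness not stated. The 56 is taken as given.

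**1. Reproduce the stated figure.** n × (1 + dropout) = 56 × 1.30 = 72.8, rounded up to 73. This matches.

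**2. Check whether 73 does its job.** Retained = 73 × (1 − 0.30) = 51.1, about 51, which is 5 short of 56. A start of 73 keeps 56 only if dropout is no more than 1 − 56/73 = 23.3%, not the 30% stated.

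**3. Correct inflation.** n / (1 − dropout) = 56 / 0.70 = 80. Check: 80 × 0.70 = 56.

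**4. Compare with the rolls**, assuming every child takes part:

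| Roll | Margin over 73 | Margin over 80 | Left after 30% loss |
|---|---|---|---|
| 82 | 9 | 2 | 57.4 |
| 119 | 46 | 39 | 83.3 |
| 121 | 48 | 41 | 84.7 |
| 155 | 82 | 75 | 108.5 |

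All four schools clear 80 and keep at least 56.

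**5. Where the wrong benchmark could mislead.** The documents give no opt-out rate, so take the range at the smallest school and assume that opt-outs come on top of the 30% dropout.

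- With 0 to 2 opt-outs (82 to 80 children), both benchmarks are met.
- With 3 to 9 opt-outs (79 to 73 children, or 3.7% to 11.0% of the roll), the printed 73 is met but 80 is not. Expected retention runs from 79 × 0.70 = 55.3 down to 73 × 0.70 = 51.1, all below 56.

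**6. Size of the power loss if only about 51 were retained.** The plan's own power figure cannot be recomputed uniquely, because the number of groups, the number of measurements and the within-child correlation are not stated. Two simple approximations, both assumed here with two-sided α = 0.05, give the scale:

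- Normal formula anchored at 95% power for n = 56 and scaled by √n: Φ(3.605 × √(51.1/56) − 1.96) = Φ(1.48) = 0.931, where 3.605 = 1.96 + 1.645.
- Two-group comparison at d = 0.70 with 51 per group: 0.942 by the normal formula (Φ(0.70 × √(51/2) − 1.96) = Φ(1.57)) and 0.938 by the t distribution.

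This gives roughly 93% to 94% against the planned 95%.

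**The case against.** The strongest reply is that nothing practical changes. The 73 is a benchmark and not a recruitment cap: every child in Groups 5 to 8 is invited, no school has as few as 73, and all four rolls exceed the corrected 80. In addition, the linear mixed models under Data analysis use every available observation, so children with incomplete follow-up still contribute.

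Most of this stands, and it limits the point. It does not make 73 right. The plan chose to inflate for dropout so as to secure 56, and the printed figure does not secure it. The mixed-model argument softens a strict reading of 51 retained children, but it was not the basis on which the 73 was derived.

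A reader might also draw stronger conclusions, which the document does not support:

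- **That the study is too small, or that the sufficiency statement fails.** With near-full participation, each school keeps at least 56 after 30% loss.
- **That power falls to 93% on the plan's own terms.** That value comes from an assumed formula. The plan's ANOVA inputs are not given, and a two-group approximation gives about 94%.
- **That a stated overall total needs correcting.** The article sets a per-school number and compares it with the 477 available; it gives no four-school sum of the 73s.
- **That children leaving after Group 8 make the margin worse.** How the dynamic cohort in Table 1 relates to natural dropout is a separate question. The 80 already carries the full 30% allowance.

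**Conclusion.** The point holds as an arithmetic error with a small consequence. Given 56 required and 30% dropout, the per-school benchmark is 80, not 73, a difference of 7 children. The conclusion that the baseline population suffices stands if nearly all children take part. At the smallest school, however, the reserve over the benchmark is 2 children rather than 9, and more than 2 opt-outs there would take it below the benchmark. The other three schools have ample room.

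This rests on three assumptions: the 56 is accepted as printed, the 30% is a share of the children who start, and opt-outs are not already inside the 30%. If opt-outs are counted within the 30%, the smallest school still keeps 57.4.

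**What to change.** In Power calculation for the primary outcome, replace 73 with 80 and show the step (56/0.70). Restate the comparison with the rolls: all four exceed 80, the smallest by 2 children, so sufficiency at that school depends on almost complete participation. Say whether parental opt-outs are included in the 30%.

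The cost is one number and one or two sentences. The restated benchmark calls for no extra recruitment and no change to the analysis.
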